### Overview of treatment

Session One covers the procedural aspects of treatment such as conditions of confidentiality, the recording of sessions, suicide risk assessment as well as guidelines for treatment and emphasising the importance of attending each weekly session. Session One also provides psychoeducation about the role of substance use in depression, explores the participant’s current situation and their ideal life, reviews the treatment rationale as well as introducing behaviour monitoring. The first session introduces the weekly homework assignment which is repeated each subsequent session. This involves the monitoring of activities on an hourly basis with the participant also providing ratings on the enjoyment and importance of each activity on a numerical scale from 1 to 10, as well as a rating of their overall daily mood from 1 to 10 (1 being low and 10 being high).

Session Two begins with the revision of substance use, depression symptoms and suicide risk, followed by a detailed review of the daily monitoring forms completed that week. This review occurs in all subsequent sessions. Enjoyment and importance ratings are considered for each activity and participants explore any difficulties that they had completing monitoring forms. The treatment rationale is reviewed prior to introducing the concept of life areas (relationships; education/career; recreation/interests; mind/body/spirituality and daily responsibilities). The majority of the session focuses on exploring the participant’s values within each of the life areas and generating activities that are associated with each life area. Finally, participants are introduced to a list of behavioural activities to assist in coping with cravings for substances. These include using delay and distract techniques, managing hunger and thirst, using controlled breathing techniques, imagery exercises such as “urge surfing”, seeking social support, and using positive self-talk.

During the third session, participants continue to generate activities that are value based for each life area. They then choose fifteen of these activities and rank them in order from easiest to hardest taking into account the level of expected enjoyment and importance of each activity. The participant is encouraged to include some activities that they are already engaged in. Session Three concludes with the introduction of the two brief behavioural techniques for managing emotional distress, these include a self-soothing exercise (where the client is asked to use their five senses to create more soothing moments in their day), and a breathing exercise where participants slow their breathing and think of the word “relax” when exhaling.

In Session Four participants revisit the activity list from the previous session and choose activities to schedule into their monitoring forms for the upcoming week. They progress from easier to harder activities and have the opportunity to reassess the order of activities throughout sessions. The process of selecting activities from their list occurs each session until the end of treatment. Participants are encouraged to choose between one and three new activities each week from a variety of different life areas. Session four ends with the introduction of a defusion exercise (e.g. using repetition or singing the thought).

Session Five introduces the concept of contracts with significant others. Participants are encouraged to select an activity that they have found difficult to complete and then select three friends or family members who may be able to assist them to complete this activity. The aim is to increase social support and increase enjoyment in completing activities. Sessions Six to Ten reinforce material previously introduced with a focus on activity selection and monitoring. In Session Six a simple grounding exercise is introduced at the end of the session (notice five things you can see, hear and feel). Similarly, at the end of Session Eight a basic mindfulness exercise is introduced for participants to practice.

Session Ten concludes treatment with a list of skills achieved and an opportunity to explore the management of potential setbacks. Throughout treatment, participants are encouraged to recognise patterns of depressed behaviour and the way in which engaging in enjoyable and important activities may impact their overall mood.

Prior to each session participants will complete the PHQ-9 [56] and be asked how many days they have used substances (alcohol, cannabis, benzodiazepines, heroin, other opiates, methamphetamine, and ‘other’) in the past week. This will enable therapists to monitor depressive symptoms and substance use throughout treatment, and help to identify unfavourable changes in symptoms. If concerned for the safety and wellbeing of the participant, the therapist will consult with the project coordinator, additional support services will be offered to the participant, and it will be determined whether or not ongoing therapy is appropriate for them. Although unlikely, any adverse events attributed to the intervention will be reported the HRECs. The participant information sheet also instructs participants to contact the project coordinator if they experience “significant distress as part of this study” and provides contact details for the ethics secretariat should they which to make a complaint about the conduct of the study.

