Active suicidality, psychosis and organic or traumatic brain injury will exclude an individual from entering the study. Suicidality is assessed by the PHQ-9 during the screening interview. Participants are asked “in the past 2 weeks/2-weeks before detox, have you been bothered by thoughts that you would be better off dead.” If participants indicate that they have been bothered by these thoughts, the research officer then probes further, using questions taken from the Suicide Assessment Kit screener [57], to determine whether these thoughts are ongoing, how long they have been having the thoughts, how intense they are, how likely it is that they will act on these thoughts in the near future, whether they have ever attempted suicide previously, and if so, how recently. Individuals who have attempted suicide in the past 6 months and for whom nothing has changed (i.e., they have received no intervention, or nothing has changed in their circumstances to reduce their risk), will be excluded from the study, and given a referral for appropriate support. If the thoughts are intense or the participant deems it likely that they will act on them in the near future, they are asked about any current plans and prior attempts, and are referred to an appropriate staff member at the treatment service for ongoing support and management.

Suicidality is assessed further as part of the baseline interview. The BDI-II and CIDI 3.0 both ask questions about suicidal thoughts, with the CIDI also asking about plans and attempts [49, 55]. Additional questions about the lifetime number of suicide attempts and recency of the last attempt are also asked. In situations where suicidality is indicated, the research officer uses the additional probing questions described above to assess their current risk, and to determine whether there is a need for exclusion from the study and referral for additional support. It is possible for a person with a current plan and thoughts of suicide to be recruited to the study provided the risk is not deemed imminent, and the treatment service is made aware of the suicidal thoughts and plan.

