#### Assessment occasions

The structured baseline interview will be administered by the research officers, followed by randomisation of participants to one of two groups; (1) TAU, or (2) Activate plus TAU (Fig. 1). The allocation sequence will be computer-generated by someone independent of the Activate team. The project coordinator will then inform the psychologist about the allocation, and they will notify the study participant. Follow-up interviews for the Activate and TAU groups will parallel each other, conducted at 3-months and 12-months post-baseline. Primary and secondary outcome measures will be assessed at all three assessment occasions, with the exception of client satisfaction, which will be assessed on completion or cessation of the Activate intervention. Follow-up interviews will be administered by the project’s research officers who will be blind to group allocation. The baseline and follow-up interviews are estimated to take 60–90 min to complete. Participants will be reimbursed AU$30 per interview for out of pocket expenses.

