### Measures

#### Baseline and follow-up interviews

The baseline and follow-up interviews will examine demographics, drug use history, treatment history (for substance use and depression), and will use validated instruments to assess a) the primary treatment outcomes of depression and substance dependence, and b) secondary treatment outcomes related to the therapy and mental health. Demographic measures will include age, gender, level of education, employment status, main source of income, marital status, living arrangements, and prison history. A drug use history (including age of first use, and the number of days used in the last 30 and 90 days), will be obtained for heroin, other opiates, methamphetamine, cocaine, hallucinogens, antidepressants, benzodiazepines, alcohol, cannabis, inhalants and tobacco. Prescription drug use will also be recorded. Drug treatment and depression treatment history will assess current treatment(s), the age at which they first sought treatment, number of times they have commenced treatment, and the recency of these treatments. Information will also be obtained on the participants’ history of suicide, self-harm, and occasions where they lost consciousness as the result of a head injury.

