#### Symptom monitoring and secondary outcome measures

The Patient Health Questionnaire-9 (PHQ-9) will be used in the initial screening interview, and then by therapists to monitor depressive symptoms among the intervention group [56]. The PHQ-9 is a nine-item screener for major depression and a measure of depression severity, which assesses the presence of each of the nine DSM-IV criteria for major depression in the preceding 2 weeks. Scores range from 0 to 27, as each of the nine items can be scored from ‘0’ (not at all) to ‘3’ (nearly every day) [56]. Major depression is indicated if 5 or more of the 9 depressive symptom criteria have been present at least “more than half the days” in the past 2 weeks, and 1 of the symptoms is depressed mood or anhedonia. The PHQ-9 has demonstrated excellent internal reliability (Chronbach’s α = 0.86–0.89), and test-retest reliability (*r* = 0.84) [56]. Criterion validity has been demonstrated in a sample of 580 primary care patients who were independently re-interviewed by a mental health professional. Receiver Operator Curve (ROC) analysis showed that the area under the curve for the PHQ-9 in diagnosing major depression was 0.95, suggesting that it discriminates well between persons with and without major depression [56].

Client satisfaction will be assessed after completion of Activate therapy using the Client Satisfaction Questionnaire, an 8-item scale designed to measure and assess client satisfaction with health and human services (CSQ-8; [64]). The CSQ-8 elicits the client’s perspective on the value of services received. Responses are given on a 4-point Likert scale. Scores range from 8 to 32, with higher scores indicating greater satisfaction. The CSQ-8 has demonstrated excellent reliability and internal consistency (Cronbach’s alpha 0.92 to 0.93) [64]. Secondary outcome measures, including those associated with behavioural activation therapy and mental health will be assessed at baseline, 3- and 12-month follow-up (Table 2).

**Table 2 Tab2:** Schedule of assessments

Domain	Measure	Screening	Baseline Pre-allocation	3 month follow-up	12 month Follow-up
*Eligibility*					
Depression symptoms	Patient Health Questionnaire (PHQ-9) [56]	+	−	−	−
Depression screener	CIDI 3.0 Depression screener questions [54, 55]	+	−	−	−
*Primary outcome measures*					
Substance dependence	CIDI 3.0 Substance dependence (past month DSM-IV TR) [54] Severity of Dependence Scale (SDS) [61]	− −	+ +	+ +	+ +

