#### Treatment as usual

The control group will receive the model of care provided in accordance with standard practice at participating RR and OST services, and will be delivered by agency staff. In addition to standard drug and alcohol treatment, clients in RR may receive additional treatment from case workers or in-house psychologists. Similarly, in addition to methadone or buprenorphine maintenance for managing heroin dependence, OST clients may also receive counselling for depressive symptoms, antidepressant medication where appropriate, and referral to mental health services when required. All treatment for depression received as a part of TAU will be recorded in participant interviews. These will be controlled for in comparative analysis of treatment outcomes.

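### The only adverse-event rule stated depends on attribution to Activate, so treatment as usual can never contribute a reported event and counts kept under it cannot be compared between arms

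*Protocol article*

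**What the plan says.** The adverse-event rule is one sentence in the protocol article, section Overview of treatment: "Although unlikely, any adverse events attributed to the intervention will be reported the HRECs". It follows a description of therapists giving the PHQ-9 and asking about substance use before each session. Of that monitoring the article says: "This will enable therapists to monitor depressive symptoms and substance use throughout treatment". The section Symptom monitoring and secondary outcome measures confirms where this applies: after screening, the PHQ-9 is used "then by therapists to monitor depressive symptoms among the intervention group".

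The comparator is described under Treatment as usual: "The control group will receive the model of care provided in accordance with standard practice at participating RR and OST services". Its delivery is by agency staff.

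The population carries suicide risk by design. The eligibility text (under the heading Sample size calculation) says: "It is possible for a person with a current plan and thoughts of suicide to be recruited to the study". The conditions are that risk is not judged imminent and that the service is informed.

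Both arms are assessed on the same schedule. Under Assessment occasions: "Follow-up interviews for the Activate and TAU groups will parallel each other, conducted at 3-months and 12-months post-baseline", by interviewers blind to allocation, and "Primary and secondary outcome measures will be assessed at all three assessment occasions", client satisfaction excepted. The section Baseline and follow-up interviews lists the participant's "history of suicide, self-harm, and occasions where they lost consciousness as the result of a head injury" among the information to be obtained.

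**The concern.** A safety count is informative in a randomised trial when an event is counted the same way in either arm. Here the stated condition for reporting is that the event be attributed to a treatment that one arm does not receive. The count therefore cannot be set against a control count. Within the Activate arm it turns on a judgement of causation, and the sentence states in advance that such events are unlikely.

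Detection points the same way. Activate participants have up to ten study contacts at which symptoms are checked. The article describes no matching study contact for control participants between the interviews.

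At stake is what the ethics committees and later readers can learn about serious events in people with depression and recent substance use, some enrolled with a current suicide plan. Serious events judged unrelated to therapy, and any that Activate prevented relative to usual care, are invisible to a count kept under this rule.

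**Working it through.** The article gives no adverse-event rate, so there is no planned figure to reproduce. The check sets the sections side by side and then adds a labelled illustration.

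**1. What the rule can yield in each arm.** The expected reported proportion is the true event rate × the probability that an event is attributed to Activate.
- Control: the attribution probability is 0, because Activate is not given. Reported proportion = true rate × 0 = 0.
- Activate: it depends on the attribution judgement. The article gives neither quantity, so both are assumed below, with the same true rate in both arms.

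| True rate, both arms | Share attributed | Reported, Activate | Reported, control |
|---|---|---|---|
| 2% | 5% | 0.1% | 0% |
| 2% | 50% | 1.0% | 0% |
| 5% | 20% | 1.0% | 0% |
| 10% | 5% | 0.5% | 0% |
| 10% | 50% | 5.0% | 0% |

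With 100 randomised per arm, 2 to 10 true events in each arm would appear as about 0.1 to 5 in Activate and none in control. The reported difference carries no information on the true difference, which is nil here. These figures count reports to the ethics committees, not events held in the trial data.

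**2. Detection between interviews.** Activate has a PHQ-9 and a substance-use question before each of ten weekly sessions, and a route from therapist to project coordinator. Control has no comparable study contact between baseline and 3 months. Neither arm has one between the end of therapy and 12 months. The information sheet tells participants to contact the coordinator if distressed. That is not limited by arm, but it relies on the participant to volunteer.

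**3. What the interviews provide in both arms.** Table 2 schedules the BDI-II and the CIDI depression section at baseline, 3 and 12 months. The eligibility text says both ask about suicidal thoughts, and the CIDI about plans and attempts too. History of suicide and self-harm is listed for the interviews. A comparison of these items by arm, free of attribution, is therefore possible. Its limits are:
- The BDI-II refers to the past 2 weeks, and the CIDI depression section was modified to the past month. On past-month windows, interviews at 3 and 12 months cover 2 of 12 months and leave 12 − 2 = 10 uncovered. The history items might fill that gap, but no recall window is given for them at follow-up.
- Suicide history is named among the secondary measures in Trial aims & hypotheses, within an aim about moderators and mediators of response. It has no row in Table 2 and is absent from the matching list in the Discussion. Nothing assigns it a role as a harm outcome.
- Interviews cannot record a participant's own death, and they miss participants not reached. Attrition of 20% is expected: 200 × (1 − 0.20) = 160 remain, or 80 per arm if losses are equal.

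**4. What an arm-neutral comparison could show.** Two-sided α = 0.05, n per arm, assumed rates p₀ and p₁ with mean p̄:

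power = Φ{ [|p₁ − p₀| − 1.96·√(2p̄(1 − p̄)/n)] / √([p₀(1 − p₀) + p₁(1 − p₁)]/n) }

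For 5% v 10% with n = 80: √(2 × 0.075 × 0.925/80) = 0.0416 and √((0.0475 + 0.09)/80) = 0.0415. This gives (0.05 − 0.0816)/0.0415 = −0.76, so power is 22%.

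| Rates | 80 per arm | 100 per arm |
|---|---|---|
| 5% v 10% | 22% | 27% |
| 5% v 15% | 56% | 66% |
| 5% v 20% | 83% | 90% |

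Only large differences would be detected reliably, so the table should describe and not test.

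**The case against.** The strongest reply is that the sentence governs notification to ethics committees. It does not say what is recorded, analysed or published, and it does not say that other events will be withheld. A reader might infer that harm cannot be compared between arms at all, or that a deterioration under Activate would go unseen. The document does not support that. Depression severity and diagnosis, and severity and diagnosis of dependence, are primary outcomes, compared by intention to treat with no attribution step. Suicidal thoughts, plans, attempts and self-harm are asked of both arms by blinded interviewers. The zero in the illustration is a count of notifications, not a loss of those data. This part of the reply stands and limits the point.

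It can also be said that unequal contact follows from a usual-care comparator chosen for stated reasons. That is fair, and it is why events found only in therapy should be kept apart instead of removing the contact.

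Lastly, this is a condensed article that refers some oversight details to an additional file not shown, and silence on deaths or admissions could be filled there. Silence alone would indeed be no finding. But the article does state a rule, it is the only one stated, and its condition excludes one arm by definition. That part of the point survives.

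**Conclusion.** The point holds in limited form. The stated reporting rule is one-sided: its control count is zero by construction, its Activate count depends on attribution, and the two cannot be compared. Between-interview detection through the study is described for Activate only. The conclusion about the rule follows from its wording and needs no assumed rate; the 0.1–5.0% against 0% rests on assumed event rates and attribution shares.

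Interview-reported suicidality and self-harm, depression and substance use remain comparable, subject to attrition, recall windows and low power for rare events. What is left without stated arm-neutral handling is deaths, overdoses and hospital admissions, together with a designated harm role for the suicidality items. The primary efficacy comparison is not affected. The change is worth making because it is cheap, removes a built-in asymmetry and serves participant safety.

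**What to change.** Replace the sentence in Overview of treatment with a rule on these lines:

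- Deaths, suicide attempts, self-harm, overdoses and hospital admissions that become known from the interviews or from follow-up tracing are recorded and reported to the ethics committees in both arms, regardless of attribution.
- These events are tabulated descriptively by randomised arm, together with the suicide and self-harm items already collected at 3 and 12 months.
- Events detected only through therapy sessions are listed separately, so that unequal contact does not enter the comparison.
- A causal judgement may still be noted for each event, but it does not decide whether the event is counted.

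The cost is somewhat more reporting to the ethics committees and one extra table. Table 1 gives recruitment as completed, so any new interview items may come too late for many participants. Tabulating what is already collected, and what tracing has revealed, remains feasible.

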#### Treatment as usual

The control group will receive the model of care provided in accordance with standard practice at participating RR and OST services, and will be delivered by agency staff. In addition to standard drug and alcohol treatment, clients in RR may receive additional treatment from case workers or in-house psychologists. Similarly, in addition to methadone or buprenorphine maintenance for managing heroin dependence, OST clients may also receive counselling for depressive symptoms, antidepressant medication where appropriate, and referral to mental health services when required. All treatment for depression received as a part of TAU will be recorded in participant interviews. These will be controlled for in comparative analysis of treatment outcomes.

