### Trial design

The Activate study is a parallel, single blind, superiority randomised controlled trial. Participants will be randomly assigned to receive either Activate (*n* = 100) or treatment as usual (TAU; *n* = 100), stratified by treatment modality (RR and OST). Treatment as usual is the comparator group, as it is clinically important to determine whether Activate adds any benefit in terms of improved depression symptomatology and reduced dependence symptoms, beyond that gained from usual care (i.e. RR or OST). Separate randomisation schedules will be used for the two treatment modalities. To reduce the risk of bias, minimisation, a dynamic random allocation technique, will be completed by someone independent of the research team using Minim-Py [48]. Gender and depression severity have been identified as significant prognostic factors and minimisation will ensure classification of participants with respect to these variables. Depression severity will be categorised according to BDI-II score, as mild (14–19), moderate (20–28) or severe (29–63) [49]. Minimisation has been shown to have both theoretical and practical validity, in particular it is considered an effective randomisation tool in clinical trials of small to moderate sample size (approximately, *N* = 200–400) with multiple prognostic factors to be considered [50–52].

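### Controlling for all depression treatment received within usual care, not only that in place at baseline, can bias the estimated effect of adding Activate

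*Protocol article*

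**What the plan says.** The Treatment as usual section describes care given by agency staff. For the opioid substitution group it says that "OST clients may also receive counselling for depressive symptoms, antidepressant medication where appropriate, and referral to mental health services when required". It continues: "All treatment for depression received as a part of TAU will be recorded in participant interviews". The next sentence sets the analysis rule: "These will be controlled for in comparative analysis of treatment outcomes".

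On timing, Assessment occasions states: "The structured baseline interview will be administered by the research officers, followed by randomisation of participants to one of two groups". It then states: "Follow-up interviews for the Activate and TAU groups will parallel each other, conducted at 3-months and 12-months post-baseline". Under Baseline and follow-up interviews, depression treatment history, including current treatment, is part of the baseline interview and of both later ones.

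Trial design justifies the comparator on the ground that "it is clinically important to determine whether Activate adds any benefit in terms of improved depression symptomatology and reduced dependence symptoms, beyond that gained"; the yardstick there is usual care in either modality. Statistical analysis promises an intention-to-treat analysis of all randomised participants, together with a per-protocol analysis.

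**The concern.** A covariate fixed before randomisation can be adjusted for safely. One that arises afterwards, and that allocation can influence, cannot be adjusted for without changing what is estimated.

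The care listed here is offered where appropriate or when required, so it follows current symptoms, and current depression is a primary outcome. If Activate lowers symptoms, it can lower the need for other depression treatment. That treatment then lies on the path from allocation to outcome, and it may also share unmeasured causes with the outcome. Holding it constant can remove part of the effect of allocation, or bring in a spurious difference between people who are alike on treatment but unlike in severity.

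At stake is the meaning of the main depression comparison. The trial asks what Activate adds to usual care as delivered. A model that holds part of usual care fixed answers another question, and a reader would not know from the result which one had been answered.

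**Working it through.** **1. Is the covariate pre- or post-randomisation?** Both. Participants are already in usual care at entry: at least 3 months for opioid substitution and at least 1 week for residential rehabilitation (Sample size calculation). The baseline interview records their current depression treatment, so that part precedes randomisation. Treatment that starts later can be recorded only at 3 and 12 months. The sentence covers both parts.

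**2. Scale of the planned comparison.** Inputs from Sample size calculation: BDI-II difference 5, SD 15, within-subject correlation 0.023, alpha 0.05, final N 160. Assumed: 80 per arm, two follow-up measures, two-sided test.

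- SD of the time average = 15 × √((1 + 0.023)/2) = 10.73
- Standard error of the difference = 10.73 × √(2/80) = 1.70
- Power for 5 points = 83.8 %, against the stated 81 %. The gap is small and has no bearing on this point.

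**3. How far can adjustment move the estimate?** In a linear model with arm and an indicator of other depression treatment,

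adjusted effect = unadjusted effect − g × (p₁ − p₀),

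where p₁ and p₀ are uptake under Activate and TAU, and g is the fitted coefficient of that treatment. The shift is zero if uptake is equal or if g is zero. Its sign depends on both.

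**4. Scenarios.** The protocol gives no uptake rate, no effect of the other treatment and no dependence on severity. All of these are assumed. Each row simulates 1,000,000 subjects with BDI-II SD about 15 (Monte Carlo error about 0.03). Inert means that the other treatment does not affect BDI-II.

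| Assumed scenario | Uptake TAU / Activate | g | Unadjusted | Adjusted |
|---|---|---|---|---|
| A. Equal uptake, severity-driven, inert | 41 % / 41 % | 4.70 | −5.03 | −5.03 |
| B. Uptake driven by baseline severity only, inert, baseline BDI-II in the model | 50 % / 28 % | 0.02 | −4.95 | −4.95 |
| C. Other treatment lowers BDI-II by 5, no shared cause | 40 % / 20 % | −4.98 | −4.02 | −5.02 |
| D. Unmeasured severity drives uptake, inert | 41 % / 22 % | 4.72 | −5.03 | −4.13 |
| E. As D, smaller uptake gap | 41 % / 31 % | 4.70 | −5.04 | −4.61 |
| F. As D, no true effect | 41 % / 22 % | 4.73 | 0.00 | +0.89 |
| G. Current severity alone drives uptake, inert, baseline BDI-II in the model | 39 % / 32 % | 10.87 | −4.95 | −4.19 |
| H. Extreme: uptake depends on arm and current severity, inert, baseline BDI-II in the model | 50 % / 24 % | 10.9 | −4.97 | −2.16 |

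Check of C: −4.02 − (−4.98)(0.20 − 0.40) = −4.02 − 1.00 = −5.02. Check of D: −5.03 − 4.72 × (0.22 − 0.41) = −5.03 + 0.90 = −4.13.

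Rows B, G and H assume a baseline-to-outcome correlation of 0.5, and G and H assume uptake odds 8 % higher per BDI-II point. With no true effect, G stays at zero because uptake is then equal, whereas H gives about +2.9. If baseline BDI-II is left out, H becomes about −1.4.

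**5. Reading the table.** C overstates the total effect by 1.0 point. D understates it by 0.9. F produces 0.9 points where there is no effect. One point is 1/1.70, or about 0.6 standard errors. The shift in H, 4.97 − 2.16 = 2.8 points, is about 1.7 standard errors.

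**The case against.** The strongest reply is that the sentence does not say during follow-up. Depression treatment is recorded at baseline as well, and participants are in usual care before randomisation, so part of the adjustment is legitimate. This stands. A reader might infer that the whole covariate is post-randomisation, and the text does not support that. But received as part of TAU, in the section that defines the comparator, points naturally to care during the trial. Nothing confines the rule to baseline.

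Second, the size is unknown. A reader might take a loss of more than half the effect, as in row H, as the expected consequence. The documents support neither the 26-point uptake gap, nor the dependence on severity, nor an inert treatment. Rows A and B show no shift at all. So the charge is that adjustment can bias the estimate, not that it will.

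Third, the route from allocation to uptake is only partly documented. No passage says that agencies give less depression care to Activate clients. When a study therapist is concerned, "additional support services will be offered to the participant" (Overview of treatment), but it is unclear that such services count as agency-delivered TAU. What remains is that need-based care can change when symptoms change, and the intervention is meant to change symptoms.

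Fourth, a reader might say that the rule revokes intention-to-treat. It does not: the analysis set is unchanged, and the article does not say whether the adjusted model is primary or supplementary. A full analysis plan might settle that. The sentence is nonetheless an unqualified commitment covering the comparison of outcomes, so the objection softens the point without removing it.

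**Conclusion.** The concern holds in a limited form. As written, the rule lets the comparison condition on need-based treatment received after randomisation, which allocation can change. That can bias the estimate of the total effect of adding Activate to usual care.

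The size depends wholly on assumptions about uptake by arm, what drives uptake, and whether the other treatment works. The scenarios give 0 points in the benign cases, about 0.4 to 1 point in moderate ones, and about 3 in an extreme one, against a planned difference of 5. The shift can go towards or away from zero, and the adjusted estimate can be non-zero when the true effect is nil. Equal uptake would remove the problem, but it cannot be relied on in advance when the intervention targets the symptoms that prompt the other treatment. The adjustment for treatment already in place at baseline is sound and need not be given up.

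**What to change.** Restrict the sentence in Treatment as usual to depression treatment recorded at the baseline interview. State that the primary intention-to-treat model adjusts only for pre-randomisation variables already collected: the baseline value of the outcome, modality, gender and, if wanted, baseline depression treatment.

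Report depression treatment received during follow-up by arm, as a description of usual care as delivered. If an analysis that uses it is wanted, label it supplementary and state its own estimand and assumptions.

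This costs one amended sentence, with a matching line in Statistical analysis. It needs no new data and leaves the sample-size inputs unchanged. It should be settled before the final-stage analyses that follow the 12-month interviews.
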